### 2.8. Statistical methods

All statistical analyses will be performed for intention-to-treat and a per-protocol population. Descriptive statistics, including mean and standard deviation, median and range, or number and percentage, will be provided for all assessed outcomes. To investigate the effects of time and groups on outcome variables, a repeated measures design with a linear mixed model will be employed. The linear mixed model will include time (baseline, 3 weeks, and 12 weeks), group (control and intervention groups), and time*group interaction as fixed effects, while sex, height, and weight will be treated as random effects. Assumptions of normality, independence, and homoscedasticity will be checked to ensure the validity of the model. Effect sizes with 95% confidence intervals will be calculated. Missing data will be handled using multiple imputation or maximum likelihood estimation. A two-tailed approach will be used. The significance level will be set at p<0.05. All statistical analyses will be conducted using SPSS (version 25.0; IBM, Armonk, NY).

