## 2. Methods

### 2.1. Study design

This study was designed as a single-blind, pilot, randomized controlled clinical trial. This protocol was developed in accordance with the Standard Protocol Items: Recommendations for Interventional Trials (SPIRIT) guidelines (S1 Table) and the TIDier checklist (S2 Table). We designed a stratified random sampling protocol and will conduct a two-arm randomized controlled trial comparing conventional rehabilitation alone with conventional rehabilitation combined with additional in-bed self-exercises based on EMG sensor feedback (Fig 1). Participants will be enrolled from a tertiary hospital and a rehabilitation hospital. This study is a pilot, randomized controlled clinical trial investigating the feasibility and safety of in-bed self-exercises and aims to recruit at least 20 participants. Assuming a 15% loss to follow-up, the required sample size was set at 24 patients (12 patients per group) to be recruited in this study. The study received approval from the Seoul National University Hospital Institutional Review Board (IRB No: D-2208-177-1354, September 21, 2023) (S1 File), and the protocol was registered and approved on the ClinicalTrials.gov (Trial record: NCT05820815).

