### 2.3. Recruitment and allocation

Participants will be recruited by posting a notice on the bulletin boards of the tertiary and rehabilitation hospital. The schedule of enrollment and assessment of the participants are shown in Fig 2. The principal investigator or researchers of this study will provide a detailed explanation of the study to the guardians or patients and will not exclude patients who are likely to participate based on their socioeconomic status. An independent researcher who is not involved in the recruitment, intervention, or evaluation of the patients will generate the allocation sequence using a web-based randomization system to ensure allocation concealment and blinding. Participants will be assigned to the control or intervention group in a 1:1 ratio using the stratified block randomization method, stratified by age and modified Rankin score. Patients will be stratified by age (<65 years and ≥65 years) and by modified Rankin Scale (2–3 and 4–5). Sequence generation will be performed using computer-generated random numbers, and the website will be used to inform the treatment provider when the intervention is assigned. Two therapists, each from a different institution, will assess the primary and secondary outcome measures. These therapists will be blinded to group allocation by blocking access to the randomization table. The patients and treatment providers are instructed not to disclose the allocation to the evaluator. The evaluator and data analyzer are blinded to the group allocation of the patients.

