**Fig 9 pone.0310178.g009:**
[figure not shown]
Pittsburgh Rehabilitation Participation Scale and newly defined exercise sessions.

The secondary outcome measures are the number and percentage of participating sessions, the number and percentage of effortful sessions, the number and percentage of successful sessions, the mean amplitude of muscle contractions in a session, and the duration and percentage of participating sessions during self-exercises. Rivermead Motor Assessment, Manual Muscle Test for muscle strength, BRS, Fugl–Meyer Assessment of the Lower Extremities, Berg Balance Scale, Functional Ambulation Category, modified Rankin scale, and Short-Form Health Survey version 2. As a muscle strength measurement test, the Manual Muscle Test is evaluated on a scale of 0–5 according to strength against gravity and resistance. In this study, the Manual Muscle Test of the hip flexor, hip abductor, knee extensor, and ankle dorsiflexor will be measured. Manual Muscle Test has good external and internal efficacy and is not dependent on examiner bias [31]. The BRS is a classification method that models the motor recovery process after stroke-induced hemiplegia on a 6-point ordinal scale. The Brunnstrom approach focuses on the unique patterns associated with stroke recovery, including spasticity development, synergistic patterns, and voluntary movements. The BRS has high inter-rater reliability (0.74–0.98) [32]. The Fugl–Meyer Assessment of the Lower Extremities investigates hip, knee, and ankle movements, and hierarchical recovery is recorded based on Brunnstrom stages of recovery from reflex to synergistic and non-synergistic movements. The Fugl–Meyer Assessment of the Lower Extremities motor domain uses a 3-point ordinal scale: 0, unable to perform; 1, partial performance; and 2, complete performance. Possible scores range from 0 to 34. The intra- and inter-rater reliabilities are excellent in early stroke patients [33]. The Berg Balance Scale was developed to objectively measure balance and fall risk in community-dwelling older adults using a three-step survey of 32 health professionals. The Berg Balance Scale examines 14 movements of daily life on a 5-point ordinal scale from 0–4, and the total score ranges from 0–56. The Berg Balance Scale is widely used to assess stroke patients, and its test-retest reliability and internal consistency are excellent [34]. The Functional Ambulation Category is a 6-point rating scale that assesses the amount of human support required when walking (with or without a personal assistive device). A score of 0 indicates a non-functional ambulator, and a score of 1–3 indicates a dependent ambulator. A score of 1 indicates the need for continuous manual contact, 2 indicate intermittent or continuous light touch, and 3 indicates supervision or verbal cues. Scores of 4–5 indicate an independent ambulator, with a score of 4 indicating independent ambulators on horizontal surfaces only and a score of 5 indicating independent ambulators on any surface, including stairs. There is good inter-rater reliability among examiners in post-stroke patients [35]. The modified Rankin scale is a widely used tool to measure global disability after stroke. The scale classifies disability from 0 (no symptoms) to 5 (severe disability). Scoring is performed by an evaluator based on patients’ functional dependence. The intra-rater reliability is excellent [36]. The Rivermead Motor Assessment consists of three sections, and sections of gross function and leg and trunk are evaluated in this study. The gross function section consists of 13 items and primarily assesses mobility from sitting to running and gait, and the leg and trunk section describes individual movements of the trunk (e.g., rolling to the affected side) and leg (e.g., ankle dorsiflexion with the leg extended while lying down). The intra-class correlation coefficients of the Rivermead Motor Assessment is between 0.88 and 0.95 [37]. The Short-Form Health Survey version 2 is a well-studied self-reported measure of functional health. The items include physical functioning, physical role limitation, pain, general medical health, vitality, social functioning, emotional role limitation, mental health, physical component scale, and mental component scale. There is good internal consistency of >0.7 for all the subscales of the questionnaire [38]. Among the assessments for the baseline status and primary and secondary outcomes, the official Korean version of the Fugl–Meyer Assessment, Berg Balance Scale, Short-Form Health Survey 36 version 2, and the Hospital Anxiety and Depression Scale will be used in this study [39–42]. The assessors who are proficient in English will conduct the English version of the assessments, including the Pittsburgh Rehabilitation Participation Scale, Rivermead Motor Assessment, Manual muscle test, Brunnstrom recovery stage, modified Rankin scale, and Functional Ambulation Category. The Short-Form Healthy Surgery 36 version 2 and the Hospital Anxiety and Depression Scale are self-administered questionnaires, and all other evaluations are clinician-administered assessments. All primary and secondary outcomes will be assessed at baseline, and at 3 weeks and 12 weeks. Assessments will be performed over two days to manage fatigue and reduce potential bias in stroke patients. The Fugl–Meyer Assessment, Berg Balance Scale, Manual muscle test, and Short-Form Health Survey 36 version 2 will be conducted on the first day, and the Rivermead Motor Assessment, Brunnstrom Recovery Stage, modified Rankin Scale, and Functional Ambulation Category will be conducted on the second day. Participants will be instructed and familiarized before the actual assessments to help them understand the evaluation processes and improve compliance. Regular breaks will be provided during assessment sessions to prevent fatigue and maintain the participants’ attention.

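### For clinical scales with a genuine baseline value, the section 2.8 model estimates change-score contrasts instead of baseline-adjusted differences, which usually costs precision and ties each estimate to chance baseline imbalance

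*Protocol article*

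**What the plan says.** Section 2.8 gives the fixed effects in one sentence: "The linear mixed model will include time (baseline, 3 weeks, and 12 weeks), group (control and intervention groups), and time*group interaction as fixed effects". The only other terms follow directly: "while sex, height, and weight will be treated as random effects". The outcome's baseline score is not a covariate, and nothing holds the two arms to a common baseline mean.

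Section 2.5.1 says of the measurements: "All primary and secondary outcomes will be assessed at baseline, and at 3 weeks and 12 weeks". For the clinical scales, the values needed for adjustment will therefore already have been collected.

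Section 2.1 describes a pilot that "aims to recruit at least 20 participants" and, allowing 15% loss to follow-up, enrols 24, or 12 per arm. In section 2.3, patients are "assigned to the control or intervention group in a 1:1 ratio using the stratified block randomization method, stratified by age and modified Rankin score". Section 2.8 sets a 5% significance level, says "A two-tailed approach will be used", and promises effect sizes with 95% confidence intervals.

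**The concern.** When baseline is one of three levels of time and both group and time*group are free, the model estimates six unconstrained means. The treatment effect at a later visit is then the interaction contrast: the later group difference minus the baseline group difference. In a randomised trial the true baseline difference is zero, so the subtracted quantity is pure noise unless it predicts the follow-up difference one for one.

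Two consequences follow:

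- The contrast generally has a larger variance than a baseline-adjusted comparison of the same data.
- It over-corrects for imbalance: the arm that starts worse by chance appears to improve more, through regression to the mean.

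With 20 to 24 patients, imbalance of a noticeable size is common. It could be mistaken for an effect of the self-exercise programme, or could hide one.

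The point is separate from which contrast or visit is primary, from whether the model has a patient-level effect, and from whether it includes the stratification factors. It would remain after all of those were settled.

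**Working it through.** **The plan's own figure.** 20 / (1 − 0.15) = 23.5, rounded up to 24, or 12 per arm. The stated sample size reproduces. The article gives no effect size, SD, correlation or power, so everything below that uses one is an assumption.

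**Which contrast the model yields.** Models with time, group and time*group were fitted to simulated complete data. With a patient random intercept, the week-3 and week-12 interaction coefficients equalled the difference between arms in mean change from baseline. Ordinary least squares gave the same at week 3. The largest discrepancy was 3e-15. With missing visits under maximum likelihood, the identity is only approximate.

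**Variance with equal SDs.** Let the SD be 1 at each visit, the baseline-to-follow-up correlation rho, and n the number per arm.

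- Change contrast: 2(1 − rho) × 2/n.
- Baseline-adjusted: (1 − rho²) × 2/n × [1 + 1/(2n − 4)], where the bracket is the cost of estimating the slope. It is 1 + 1/20 = 1.05 for n = 12 and 1 + 1/16 = 1.0625 for n = 10.
- Ratio: (1 + rho)/2 times the bracket.

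Power is from the noncentral t distribution, two-sided 5%, for an assumed 1 SD difference, with 2n − 2 and 2n − 3 degrees of freedom. Results for n = 12:

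| rho | 2(1 − rho) | (1 − rho²) × 1.05 | Ratio | 95% CI half-width (SD), change → adjusted | Power, change → adjusted |
|---|---|---|---|---|---|
| 0.3 | 1.40 | 0.956 | 0.68 | 1.00 → 0.83 | 51% → 67% |
| 0.5 | 1.00 | 0.788 | 0.79 | 0.85 → 0.75 | 65% → 75% |
| 0.7 | 0.60 | 0.536 | 0.89 | 0.66 → 0.62 | 86% → 89% |
| 0.9 | 0.20 | 0.200 | 1.00 | 0.38 → 0.38 | no gain |

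For n = 10 the ratios are 0.69, 0.80, 0.90 and 1.01, and power at rho = 0.5 goes from 56% to 66%. Simulated variance ratios (20,000 trials per setting) agreed: 0.68, 0.79, 0.89 and 1.00 for n = 12, and 0.71, 0.80, 0.91 and 1.02 for n = 10. For a smaller assumed difference of 0.5 SD, with n = 12 and rho = 0.5, power goes only from 22% to 26%.

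**Variance with unequal SDs.** If the follow-up SD is k times the baseline SD, the ratio for n = 12 is k²(1 − rho²) × 1.05 / (1 + k² − 2k·rho).

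- k = 0.8, rho = 0.5: 0.64 × 0.75 × 1.05 / 0.84 = 0.60.
- k = 1.25, rho = 0.5: 1.5625 × 0.75 × 1.05 / 1.3125 = 0.94.
- k = 1.25, rho = 0.7: 1.5625 × 0.51 × 1.05 / 0.8125 = 1.03.
- k = 1.25, rho = 0.8: 1.5625 × 0.36 × 1.05 / 0.5625 = 1.05.

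**Dependence on imbalance.** Under simple randomisation, the baseline mean difference has SD √(2/12) = 0.41, or √(2/10) = 0.45 with 10 per arm. An imbalance above 0.5 SD then arises in about 22% or 26% of trials. With equal SDs, the change contrast shifts by −(1 − rho) times the imbalance; at rho = 0.5, an imbalance of 0.41 SD moves it by 0.20 SD. Its simulated correlation with imbalance (10 per arm) was −0.58, −0.51, −0.39 and −0.21 for rho = 0.3, 0.5, 0.7 and 0.9. For the adjusted estimate it was about 0.

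In null trials with n = 12 and rho = 0.5, the test on change rejected in about 5% overall and in about 9% of trials with imbalance above 0.41 SD. Such trials are about 32% of the total, so the rest reject in about (5 − 0.32 × 8.8)/0.68 = 3.2%.

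**The case against.** **It is a choice about efficiency, and the analysis is valid.** This stands. The change contrast is unbiased over randomisation and holds its 5% level. A reader might take the 9% rejection rate as inflated type I error. It is not: the rate is conditional on a subset of trials and is offset by a lower rate in the others.

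**It does not reach every outcome.** This also stands. From the statement in section 2.5.1, a reader might infer that all outcomes have a usable baseline. But the session outcomes describe self-exercise sessions that have not begun at baseline. Section 2.5.1 also defines the PRPS categories by percentages of such sessions, and the Discussion ties the PRPS to EMG activity during self-exercise. The primary outcome is covered only if it is rated by a clinician before the intervention.

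**The size, and sometimes the direction, is unknown.** This stands in part. The article gives no correlation and no SDs. Equal SDs are an assumption, and with more spread at follow-up and a high correlation there is no gain or a small loss. That loss is at most about 5% of variance in the settings examined, whereas the possible gain is much larger.

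**Stratification limits imbalance.** True in part. Blocking on modified Rankin Scale and age groups reduces imbalance on related scales, so 0.41 SD is an upper guide. The precision argument does not depend on it.

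**The variance comparison presumes a suitable within-patient covariance and a named contrast.** Correct, and section 2.8 should be clear on both. Repairing them leaves this point in place. If the group difference at each visit were read from the model instead, it would be a follow-up-only comparison, also unadjusted; its correlation with imbalance in the simulation (10 per arm) was +0.31 to +0.90.

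**It is a pilot.** The Background nevertheless states a formal null and alternative hypothesis, and section 2.8 commits to a significance level and interval estimates. The precision of those intervals matters.

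**Conclusion.** The point holds for the Rivermead, Fugl-Meyer, Berg and SF-36 scores, and for the PRPS only on the condition above. For these, the stated model produces change-score contrasts with complete data, and they depend on the realised baseline imbalance.

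With equal SDs and 12 per arm, adjustment would cut the variance by about 32%, 21% and 11% at rho = 0.3, 0.5 and 0.7, and by nothing at 0.9. A follow-up SD below the baseline SD makes the gain larger. A follow-up SD 1.25 times baseline makes it small at rho = 0.5, and nil or slightly negative from 0.7 upward. These ranges rest on assumed correlations and SD ratios, complete data and a correctly modelled within-patient covariance.

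The documents do not support a claim that the planned analysis is biased, that its overall error rate is wrong, or that every outcome is affected. The change is worth making because the data are already collected and the cost is very small.

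**What to change.** In section 2.8, for each outcome with a genuine pre-intervention value, use weeks 3 and 12 as the only response visits. Take the outcome's baseline value, time, group and time*group as fixed effects, and report the adjusted group difference with its 95% confidence interval at each visit.

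A near-equivalent alternative keeps three visits but gives both arms a common baseline mean. It must be coded with group-by-visit terms for weeks 3 and 12 only. Deleting the group term while keeping a factor-coded time*group does not impose the constraint: the design still has rank 6, so the baseline difference stays free.

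Leave the baseline term out for self-exercise session outcomes, and state whether the PRPS has a clinician-rated baseline value.

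The cost is one rewritten sentence, a change to the SPSS syntax and about one error degree of freedom per model, with no new data or patients. The covariate form needs the baseline value to be present; the common-baseline form also keeps patients whose baseline is missing.

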### 2.5. Outcome measures

#### 2.5.1. Primary and secondary outcome measures

The baseline clinical characteristics will be collected as follows: age, sex, dominant hand, presence or absence of other diseases (high blood pressure, diabetes, hyperlipidemia, atrial fibrillation, Charlson comorbidity index), level of education; caregiver (spouse, children, others), National Institutes of Health Stroke Scale score, stroke treatment (thrombolysis/thrombectomy), stroke onset (day), lesion type (infarction, hemorrhage), lesion location (supra-tentorial, infra-tentorial), lesion laterality (right, left), stroke causes (TOAST classification: large-artery atherosclerosis/small-vessel occlusion/cardioembolic/other determined etiology/undetermined etiology), medicines for depression, spasticity, and epilepsy, Mini-Mental State Examination score, motor-evoked potential, Hospital Anxiety and Depression Scale score, and orthosis.

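### The mixed model names sex, height and weight as its random effects and no participant term; if those terms are the whole model, the group test is anti-conservative and the time-by-group test conservative

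*Protocol article*

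**What the plan says.** Section 2.8 (Statistical methods) states that "a repeated measures design with a linear mixed model will be employed". The fixed part is time at three levels, group at two, and their interaction. For the random part, the only terms given are three patient characteristics: "while sex, height, and weight will be treated as random effects". The section adds that "Assumptions of normality, independence, and homoscedasticity will be checked to ensure the validity of the model", without saying whether independence refers to observations or to residuals. Testing is two-sided at 0.05 and the software is SPSS 25.

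Section 2.5.1 fixes the repeated structure: "All primary and secondary outcomes will be assessed at baseline, and at 3 weeks and 12 weeks". The baseline data list in the same section opens with "age, sex, dominant hand, presence or absence of other diseases" and continues through stroke, comorbidity and cognitive variables. It includes sex but neither height nor weight.

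No participant effect, subject identifier or covariance across visits is named in the article.

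**The concern.** Three measurements on one patient are correlated. A mixed model has to carry that correlation somewhere, either in a participant random effect or in a residual covariance across visits. Here the random part is given to three characteristics that cannot do this job properly. Sex has two levels, so its variance component is practically inestimable. Height and weight are continuous measurements, not units sampled from a population of units. They are also missing from the listed baseline data.

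If nothing else models the patient, the errors run in opposite directions. The group main effect is tested as if there were three times as many independent observations as patients, so its interval is too narrow. The time-by-group contrast compares a patient with himself or herself, but is judged against the full between-patient scatter, so its interval is too wide. Section 1 states a formal between-group hypothesis on the Pittsburgh Rehabilitation Participation Scale, and Section 2.8 promises effect sizes with 95% confidence intervals. Those estimates and intervals are what a pilot of this size passes on to a later trial.

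**Working it through.** **Inputs from the article.** Three visits (2.5.1, 2.8); two groups of 12 (2.1); two-sided alpha 0.05 (2.8).

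**Assumed, because the article gives no value.** Equal correlation rho between any two visits of a patient, shown at 0.3, 0.5 and 0.7, and a common variance s² at each visit.

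**The plan's own figure.** A target of 20 with 15% loss gives 20 / (1 − 0.15) = 23.53, rounded up to 24. The stated 24 is reproduced. It does not rest on this model, so the sample size is unaffected.

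**Closed form when the within-patient correlation is left out.**

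- Group main effect: the mean of a patient's three visits has variance s²(1 + 2·rho)/3, whereas independence assumes s²/3. The true variance is (1 + 2·rho) times the assumed one, so type I error = 2[1 − Φ(1.96/√(1 + 2·rho))]. The interval has 1/√(1 + 2·rho) of its correct width.
- Time-by-group contrast of one visit against baseline: a patient's change has variance 2s²(1 − rho), whereas independence assumes 2s². Type I error = 2[1 − Φ(1.96/√(1 − rho))]. The interval is 1/√(1 − rho) times its correct width. If the correct model has 80% power, the effect is 1.96 + 0.8416 = 2.8016 true standard errors, and the power becomes Φ(2.8016 − 1.96/√(1 − rho)).

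| rho | Group: type I error | Group: CI width ÷ correct | Time×group: type I error | Time×group: CI width ÷ correct | Time×group: power (80% if correct) |
|---|---|---|---|---|---|
| 0.3 | 0.121 | 0.79 | 0.019 | 1.20 | 68% |
| 0.5 | 0.166 | 0.71 | 0.006 | 1.41 | 51% |
| 0.7 | 0.206 | 0.65 | 0.0003 | 1.83 | 22% |

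Example at rho = 0.5: 1.96/√2 = 1.386, giving 0.166; 1.96/√0.5 = 2.772, giving 0.006; Φ(2.8016 − 2.772) = Φ(0.030) = 0.51.

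**Check by REML simulation.** 12 per arm, three visits, 400 replicates per setting, no true effect, and sex, height and weight unrelated to the outcome. The 3-week contrast is shown.

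| Random part fitted | rho | Group: type I error | 3-week×group: type I error | Mean CI width, 3-week×group (SD units) |
|---|---|---|---|---|
| Sex as factor, height and weight as covariates | 0.5 | 0.185 | 0.007 | 2.22 |
| | 0.7 | 0.220 | 0.003 | 2.20 |
| Sex, height and weight all as factors | 0.5 | 0.122 | 0.040 | 1.69 |
| | 0.7 | 0.155 | 0.035 | 1.32 |
| Random participant intercept | 0.5 | 0.037 | 0.040 | 1.64 |
| | 0.7 | 0.050 | 0.043 | 1.28 |

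The Monte Carlo standard error near 0.05 is √(0.05 × 0.95/400) = 0.011. The first reading agrees with the closed form. In the second, nearly unique heights and weights partly stand in for a participant identifier. That rescues the interaction test but leaves the group test inflated. The participant intercept gives values close to nominal for both tests.

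**The case against.** The strongest reply is that the article calls this a repeated measures design. In SPSS MIXED the correlation across visits can be set through a REPEATED residual covariance by subject, without any participant random effect. The subject identifier, the covariance structure and the degrees of freedom are details that a condensed article may leave to an analysis plan, so their absence alone would prove nothing. All of this stands. A reader might infer that the repeated measures are certainly ignored and that every p-value and interval is wrong in both directions. The article does not support that. With a REPEATED structure by participant the correlation is handled, and with height and weight as random factors the interaction test is near nominal.

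Nor should the interaction test be said to lose most of its power without qualification. That holds near a correlation of 0.7. At 0.3 the fall is from 80% to 68%, and the article gives no correlation.

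It is also fair that this is a pilot whose sample size does not depend on the model. The missing height and weight in the baseline list are a minor inconsistency and do not show that they will go unmeasured.

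The reply does not rescue the clause itself. An analysis plan could supply the missing subject structure, but sex, height and weight would still be wrongly cast as random effects. The planned check of independence does not repair this either, because no remedy is tied to it.

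**Conclusion.** The point holds in conditional form. The misspecification of the random effects is stated in Section 2.8 and does not depend on anything unseen. Its numerical effect does. The inflated group test (about 0.12 to 0.21) and the conservative time-by-group test (about 0.02 to below 0.001) apply if the listed terms are the whole model, height and weight enter as random covariates, and the within-patient correlation lies between 0.3 and 0.7 with equal correlation across visits. With height and weight as random factors, only the group test is clearly inflated (0.122 and 0.155 at correlations of 0.5 and 0.7). With a covariance by participant, the correlation is accounted for.

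A reader might also go on to infer a multiplicity problem from the several tests that the model yields. That is a separate question: the article nowhere says that success on any one of them would count, and the choice of contrast may be fixed elsewhere.

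**What to change.** Replace the random-effects clause in Section 2.8 with wording such as: *Participant will be the subject. Correlation between the three visits will be modelled by a random participant intercept or by a within-participant residual covariance across visits. Sex, height and weight, if retained, will be fixed covariates.* State which of the two structures is used. If height and weight stay, add them to the baseline data list in Section 2.5.1; otherwise drop them.

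The fixed part can remain as it is. Treating baseline as a covariate, or naming one visit as the primary contrast, is a separate choice for the trial team and is not needed for this repair.

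The cost is wording and SPSS MIXED syntax. The sample size of 24, the visits and the assessments do not change, apart from recording height and weight if they are kept and not already collected.
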